## **6.4 Sample Size Calculation**

All exploratory analysis will test the hypothesis of greater response rate in Arm A than that in Arm B. With an estimated sample size of 30 (ARM A) and 45 (ARM B) in each group, we can estimate the response rate with a standard error no larger than 0.09 and 0.07, respectively. We will have sufficient statistical power to detect the difference between groups only if the difference between groups is sufficiently large. For example, with the sample size of 30 and 45 for Arm A and Arm B, we will have 79% power to detect the response rate of 0.25 and 0.05 between the two arms with one-sided 10% type I error rate using the continuity corrected chi-square test.

We will have more than 80% power to detect the difference between Arm A and Arm B using the log-rank test when the median PFS is 4 months and 2 months for the two arms, respectively.

In addition, in Group 1A, we will estimate the proportion of patients who are initially unresectable (as deemed by two surgeons) but converted to resectable (as deemed by two surgeons) after 8 weeks of the matched treatment, or if ever resected. With 30 patients, we expect to see at least one patient becomes resectable with a probability of 0.79, 0.96, and 0.99 if the conversion rate is 0.05, 0.10, and 0.15, respectively. We expect to see at least 2 patients become resectable with a probability of 0.82 and 0.95 if the conversion rate is 0.10 and 0.15, respectively. One-sided nominal level at 10% will be used to declare statistical significance. No P value adjustment for multiplicity will be applied due to the exploratory nature of the study. All study results need to be confirmed by future studies with larger sample sizes.

- The response rate (proportion of patients reaches CR or PR) will be estimated based on RECIST for each patient group and each treatment arm.
- The tumor regression rate (in %) will be calculated by the percent tumor size reduction from baseline to after treatment will be determined in and across patient groups.
- Progression-free survival (PFS) and overall survival (OS) will be determined in and across patient groups and treatment arms.
- The results of PFS and OS outcomes will be described relative to historical controls or published data. Due to the potential difference in patient populations between the current study and historical controls, we will also perform multivariate analyses to adjust the difference in prognostic factor(s) when comparing the PFS and OS between the different cohorts.
- The treatment grade 3-5 adverse events will be documented and analyzed by descriptive statistics.

As described earlier, this is a feasibility and descriptive study that will generate preliminary data for designing future studies. The exact numbers of patients in Arm A and Arm B for each group correspond to the feasibility endpoints. Although these numbers are unknown in the design stage, with the comprehensive genomic profiling and dedicated efforts in finding and securing the matched therapy, we expect that 40% of the patients (N=30) will be in Arm A and 60% of the patients (N=45) will be in Arm B for all three patients groups.

## **6.5 Planned Analyses**

This primary statistical analysis is descriptive in nature. Summary statistics such as the frequency counts for the categorical variables and minimum, maximum, median, mean, and standard deviation for continuous variables will be computed. The Kaplan-Meier curve will be computed to estimate the survival rate for time-to-event endpoints. Estimation with both point estimator and 95% confidence estimation for the study endpoints will be provided. Hypothesis testing with appropriate statistical methods will be performed as indicated. For example, Fisher's exact test and chi-square test will be applied to test equal proportion among groups for categorical data such as the response status. Two-sample t-test and Wilcoxon rank sum test will be used to describe the distribution of continuous variable such as the tumor regression percentage between two independent groups. Analysis of variance (ANOVA) and Friedman's test will be applied to describe the distribution of continuous variable among 3 or more groups. Log-rank test and Cox regression model will be applied for comparing the time-to-event endpoints between groups. However, due to the moderate size of the study, the statistical analysis is primarily exploratory rather than definitive. The information gathered in this exploratory study will be used for designing future confirmative studies.

The primary and secondary are for feasibility and will be estimated based upon four parameters:

### **Primary Endpoint:**

- To determine the proportion of patients who receive molecularly targeted matched treatment based on genomic analysis.

### **Secondary Endpoints:**

- We will determine the proportion of patients who consent to enroll out of those approached for study participation.
- We will determine the time of consent to physician receipt of Foundation Medicine's FoundationOne™ genomic analysis.
- We will determine the proportion of patients with actionable alterations identified in the groups (Groups 1-3), and the entire study population

The point estimate and the 95% confidence interval estimation on the proportions will be computed. For the time to consent to receiving the genomic analysis, the distribution including the mean, standard deviation, minimum, 25th percentile, median, 75th percentile, and maximum will be computed. One dimensional distribution plot will be constructed to further characterize the time distribution.

### **6.6 Exploratory Analyses**

Exploratory analyses will be conducted to evaluate efficacy and adverse event outcomes in each group and ARM and for comparison across groups.

All exploratory analysis will test the hypothesis of greater response rate in Arm A than that in Arm B. With an estimated sample size of 30 (ARM A) and 45 (ARM B) in each group, we can estimate the response rate with a standard error no larger than 0.09 and 0.07, respectively. We will have sufficient statistical power to detect the difference between groups only if the difference between groups is sufficiently large. For example, with the sample size of 30 and 45 for Arm A and Arm B, we will have 79% power to detect the response rate of 0.25 and 0.05 between the two arms with one-sided 10% type I error rate using the continuity corrected chi-square test.

We will have more than 80% power to detect the difference between Arm A and Arm B using the log-rank test when the median PFS is 4 months and 2 months for the two arms, respectively.

In addition, in Group 1A, we will estimate the proportion of patients who are initially unresectable but converted to resectable after 8 weeks of the matched treatment, or if ever resected. With 30 patients, we expect to see at least one patient becomes resectable with a probability of 0.79, 0.96, and 0.99 if the conversion rate is 0.05, 0.10, and 0.15, respectively. We expect to see at least 2 patients become resectable with a probability of 0.82 and 0.95 if the conversion rate is 0.10 and 0.15, respectively. One-sided nominal level at 10% will be used to declare statistical significance. No P value adjustment for multiplicity will be applied due to the exploratory nature of the study. All study results need to be confirmed by future studies with larger sample sizes.

- The response rate (proportion of patients reaches CR or PR) will be estimated based on RECIST for each patient group and each treatment arm.
- The tumor regression rate (in %) will be calculated by the percent tumor size reduction from baseline to after treatment will be determined in and across patient groups.
- Progression-free survival (PFS) and overall survival (OS) will be determined in and across patient groups and treatment arms.
- The results of PFS and OS outcomes will be described relative to historical controls or published data. Due to the potential difference in patient populations between the current study and historical controls, we will also perform multivariate analyses to adjust the

difference in prognostic factor(s) when comparing the PFS and OS between the different cohorts.

- The treatment grade 3-5 adverse events will be documented and analyzed by descriptive statistics.

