| Duration of administration            | 
Arm A
 
 
• Groups 1 and 2 = <math>\sim 8</math> week cycles of a regimen of <math>\geq 1</math> drug that targets molecular alteration(s) followed by disease appropriate imaging (i.e., PET-CT vs. CT vs. MR imaging) followed by crossover to treating physician's choice of systemic chemotherapy for SD or PD per RECIST, or unacceptable toxicity but to remain on I-PREDICT recommended regimen if CR, PR by RECIST 1.1
 
• Group 3 = <math>\sim 8</math> week cycles of a regimen of <math>\geq 1</math> drug that targets molecular alteration(s) followed by disease appropriate imaging (i.e., PET-CT vs. CT vs. MR imaging) with cessation of therapy if PD or unacceptable toxicity
 
 
Arm B
                                                                                                                                                                                                                                                                                                                                                                                                                                                                                                                                |

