|                         | 
1. treating physician's choice of traditional systemic chemotherapy = ~ 8 week cycles for Groups 1, 2, and 3.
 
Continue until:
 
 
• Progressive disease
 
• Unacceptable toxicity
 
• Complete response x 6 months
 
• Deemed resectable
 
                                                                                                                                                                                                                                                                                                                                                                                                                                                                                                                                                                                                                                                                                                                                                                                                                                                                                                                                                                                                                                                                                                                                                                                                                                                                                                                                                                                                                                                                                                                                         |

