| Statistical Methodology | 
Groups 1, 2, and 3:
 
 
• Determine the feasibility of the genomic-based individualized targeted therapy in patients with incurable malignancies in all patients and in each of the patient groups.
 
• Determine the response rate [(biochemical = tumor markers; radiographic = RECIST)]
 
• Determine the tumor regression rate (%) among groups in order to determine if there is a higher rate in the treatment-naïve groups (i.e., Groups 1 and 2) than in the previously treated group (Group 3)
 
• Determine progression-free survival (PFS) and overall survival (OS)
 
• Determine serious adverse events
 
 
Group 1 and Group 2:
 
 
• The treatment efficacy in the matched cohorts (i.e., Groups 1A and 2A) and the cohort of patients receiving treating physician's choice of traditional systemic chemotherapy [e.g., no drug(s) available for target(s), no insurance coverage for recommended drug(s) = Group 1B and 2B, respectively] will be described.
 
• For the unresectable patients, determine the resectability rate in Groups A and B at 8 weeks and if ever resected.
 
 
Group 3:
 
 
1. For patients in 3A and 3B, we will assess the PFS of the last unmatched therapy (PFS1) versus the PFS of the current therapy (PFS2). We will estimate the percent of patients with PFS2/PFS1 > 1.5.
 
2. The treatment efficacy in the matched cohort (i.e., matched cohort = 3A) and the cohort of patients receiving treating physician's choice of traditional systemic chemotherapy [i.e., no drug(s) available for target(s), no insurance coverage for recommended drug(s) = Group 3B] will be described.
 
 |

|  |  |
|--|--|
|  |  |
|--|--|

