Designing such a trial is complicated because one must take into consideration conventional therapies. **However, the I-SPY trial in breast cancer has already set the precedent for introducing novel, and even experimental drugs, into patients with newly-diagnosed, high-risk breast cancer. In that trial, MammaPrint is used to define high-risk; a high-risk test result means that the cancer has a 29% risk of relapsing within 10 years without any additional treatments after surgery.** However, I-SPY uses Bayesian statistics to allocate patients to treatment. As a result, a patient with a BRCA mutation may or may not receive a PARP inhibitor despite our knowledge that these work in this patient population. With the I-PREDICT trial, we propose the use of molecular profiling (FoundationOne™ assay) and matching patients to drugs based on the target(s) that exist in their tumor. For this trial, we will employ a more conservative definition of high-risk than was used in I-SPY. That is, patients who have a 50% or higher risk of death within two years (as estimated by their physician and according to 2014 NCDB data in Figure 1), or patients that already have locally advanced or metastatic disease at the time of initial diagnosis. Thus, the I-PREDICT clinical trial employs an innovative method to estimate potential efficacy of therapeutics in order to guide the choice of therapies for each individual patient in the early or late phases of disease. This trial addresses unmet needs.

We hypothesize the following:

- Obtaining treatment with targeted therapy after the treating physician receives recommendations based upon actionable genomic alteration(s) will be feasible for treatment naïve patients.
- Patients who receive targeted therapy based upon recommendations from actionable genomic alteration(s) will yield anti-tumor activity.
- Eight-week regression rates will be higher in treatment naïve patients than in previously treated patients.
- Overall survival in treatment naïve patients will be greater than expected according to historical controls matched for stage and other known prognostic factors.
- In previously treated patients, the progression-free survival on matched therapy will be greater than on their last unmatched therapy.
- Patients who receive targeted therapy based upon recommendations from actionable genomic alteration(s) will demonstrate conversion of unresectable to resectable disease.

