#### **Exploratory Endpoints**

Estimate the:

1. Overall response rate (ORR) defined as partial (PR) or complete response (CR) occurring at any point during treatment according to Response Criteria in Solid Tumors (RECIST) 1.1 in all treatment groups
2. Regression rate as a percent defined by best percent size reduction in target lesions from baseline to discontinuation in all groups
3. Progression free survival (PFS) defined as time from first dose to disease progression or death, whichever occurs first
4. Overall survival (OS) defined as time from first dose to death due to any cause
5. Resection rate as a percent of patients previously considered unresectable that are able to be resected in all groups
6. Change in biochemical tumor markers of disease as defined as the best percent change from baseline in relevant tumor markers from first dose to discontinuation
7. Incidence of serious adverse events in all groups according to CTCAE v4.03

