### **Study Group 1 and Group 2 (treatment naïve)**

ARM A:

A matched treatment regimen will be administered for approximately 8 weeks as dictated by recommendations for approved anti-cancer agents or as dictated by clinical trials. Disease-appropriate imaging (i.e., PET-CT vs. CT vs. MR imaging) will be performed at approximately week 8 according to standard of care or required clinical trial practices. Objective tumor response will be determined according to RECIST v1.1 and this First Response assessment will guide subsequent treatment according to the following:

3. Patients demonstrating a PR or CR per RECIST 1.1 will continue treatment until
  - a complete response persists for at least six months
  - the tumor becomes resectable
  - their tumor response declines to SD or PD
  - they experience unacceptable toxicity.

4. Patients demonstrating SD or PD per RECIST 1.1 will be removed from matched therapy and placed onto the treating physician's choice of systemic chemotherapy appropriate to their disease. Alternatively, the treating physician may continue matched therapy at their discretion if there are no effective traditional systemic chemotherapy regimens available.

Patients who experience SD but short of PR while on matched treatment may, after experiencing progressive disease while receiving treating physician's choice of systemic chemotherapy appropriate to their disease, return to their prior matched treatment and will be monitored again for benefit. The degree of objective tumor response observed at the patient's First Response Assessment on the original matched treatment, will then guide subsequent treatment according to the following:

1. Patients demonstrating a 10-29% decrease in the sum of diameters of target lesions (First Response Assessment) will resume treatment with the original matched treatment regimen. Treatment will continue until:
  - a complete response persists for at least 6 months,
  - their tumor becomes resectable,
  - they experience progressive disease (PD), or
  - they experience unacceptable toxicity.
2. Patients demonstrating a <10% decrease in the sum of diameters of target lesions (First Response Assessment) will then receive the traditional second-line standard of care treatment appropriate for their disease.

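### Tumor regression is defined at three different time points, and with Group-specific stopping rules the choice can create or reverse the naïve versus previously treated difference

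*Protocol*

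**What the plan says.** Three places set the time point of the same variable.

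- **Hypothesis** (Section 1.3, Rationale): "Eight-week regression rates will be higher in treatment naïve patients than in previously treated patients".
- **Endpoint** (Section 1.5, and the same definition in the Study Summary): "Regression rate as a percent defined by best percent size reduction in target lesions from baseline to discontinuation in all groups".
- **Analysis** (Section 6.6, and the same sentence in Section 6.4): regression "will be calculated by the percent tumor size reduction from baseline to after treatment". No scan is named.

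The variable feeds a planned comparison. The Study Summary states the aim: "Determine the tumor regression rate (%) among groups in order to determine if there is a higher rate in the treatment-naïve groups", set against Group 3. Section 6.3 uses regression percentage as its example for the t-test and Wilcoxon test. Sections 6.4 and 6.6 set a one-sided nominal 10% level without multiplicity adjustment.

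The end of treatment depends on the Group and arm.

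- **Groups 1A and 2A** (Section 3.2): "Patients demonstrating SD or PD per RECIST 1.1 will be removed from matched therapy" at the first assessment, about week 8, unless no effective chemotherapy exists and the physician continues. Responders stop, among other reasons, when "their tumor response declines to SD or PD".
- **Group 3A** (Study Summary): imaging follows each cycle, "with cessation of therapy if PD or unacceptable toxicity".
- **Arm B** (Study Summary): treatment runs to progression, unacceptable toxicity, resectability or "Complete response x 6 months".

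**The concern.** Week-8 change, best change and end-of-treatment change are different measurements. An analyst working from Section 1.3, 1.5 or 6.6 would produce three different results for the only directional hypothesis on regression.

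The difference between them is not the same in every Group. A Group 1A or 2A patient with stable disease normally leaves matched therapy at about week 8 without having progressed. A patient treated until progression has, by definition, regrown from the smallest sum or has new disease. An end-of-treatment value therefore records the former near the first scan and the latter after regrowth. A best value also favors whoever stays on treatment longer, because more scans give more chances of a low reading. Either measure can show a gap between Groups that comes from the stopping rule and not from the tumors.

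**Working it through.** The protocol gives no power, sample size or expected value for regression, so there is no figure to reproduce. Two checks apply.

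**1. One patient, from the progression rule.** Appendix A, Section 2.2.1 defines progression in target lesions as a sum at least 20% above the smallest on study, with an absolute rise of at least 5 mm. For a best fractional reduction *b*, the change from baseline at exactly that threshold is 1.2 × (1 − *b*) − 1.

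- *b* = 10%: 1.2 × 0.90 − 1 = +8%
- *b* = 20%: 1.2 × 0.80 − 1 = −4%
- *b* = 29%: 1.2 × 0.71 − 1 = −14.8%

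The sign turns when 1.2 × (1 − *b*) > 1, that is when *b* < 1 − 1/1.2 = 16.7%. For baseline sums under 30 mm the 5 mm rule governs and the turning point is 5 mm divided by the baseline sum: 5/20 = 25% at 20 mm and 5/25 = 20% at 25 mm.

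**2. Group means, illustrative simulation.** Tumor kinetics were made identical under two stopping rules, with 200,000 patients per setting.

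Assumptions, none of them from the protocol:

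- The week-8 change is normal with the mean shown and SD 25 points.
- Later log-growth per 8-week scan has mean 0.05 or 0.10 and SD 0.12.
- Only target lesions count, with the 20% criterion alone.
- There are no stops for toxicity, resection or sustained complete response.
- The after-treatment value is the last on-treatment scan.

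The first figure in each cell is the Group 1A/2A rule (stop at stable or progressive disease). The second is stopping at progression only.

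| Mean week-8 change | Growth | Week 8 | Best | Last |
|---|---|---|---|---|
| −5% | 0.05 | −5.1 / −5.0 | −5.6 / −9.3 | −3.4 / +10.0 |
| −5% | 0.10 | −4.9 / −5.0 | −5.1 / −6.5 | −2.8 / +14.7 |
| −10% | 0.05 | −10.0 / −10.1 | −10.7 / −14.5 | −7.8 / +5.3 |
| −10% | 0.10 | −9.9 / −10.0 | −10.1 / −11.6 | −7.1 / +10.3 |
| −20% | 0.05 | −20.0 / −20.0 | −21.0 / −24.4 | −16.5 / −4.5 |
| −20% | 0.10 | −20.0 / −19.9 | −20.4 / −21.5 | −15.4 / +0.5 |
| −30% | 0.05 | −30.0 / −30.0 | −31.5 / −34.1 | −25.1 / −15.4 |
| −30% | 0.10 | −29.8 / −30.0 | −30.3 / −31.4 | −23.4 / −10.7 |

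With no true difference:

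- **Week 8:** no gap beyond simulation noise.
- **Best:** a gap in favor of stopping at progression, from 1.1 points (31.4 − 30.3) to 3.8 points (14.5 − 10.7).
- **Last:** a gap in favor of the Group 1A/2A rule, from 9.7 points (25.1 − 15.4) to 17.5 points (14.7 + 2.8).

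The false advantage thus points in opposite directions under best and last. These gaps compare one rule with the other. If whole Groups are compared, with 40% of naïve patients in Arm A as Section 6.2 expects and everyone else treated to progression, they shrink to 0.4 of their size: 0.4 × 9.7 = 3.9 to 0.4 × 17.5 = 7.0 points for last, and 0.4 × 1.1 = 0.4 to 0.4 × 3.8 = 1.5 points for best.

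**The case against.** The strongest reply is that Section 1.5 holds the only explicit definition, that Section 1.3 is rationale, and that the bullet in Sections 6.4 and 6.6 is a garbled sentence which may mean any post-baseline scan. On that view there is one definition and some loose wording, for an exploratory endpoint whose results the protocol says need confirmation. An analysis plan that is not at hand might also name the scan.

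Part of this stands. The endpoint is exploratory, and nothing primary or secondary depends on it. But the document does not leave the time point open; it fixes it in conflicting ways, and a later plan would have to depart from some of them. Nor would following Section 1.5 test the week-8 hypothesis.

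Two stronger readings are tempting and are not supported.

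- A reader might infer that an after-treatment value measures most patients at progression. The protocol does not say so, and Section 3.2 points the other way for Groups 1A and 2A. In the simulation about 28% to 45% were at progression under that rule. The share exceeded 99% only where progression was the sole reason to stop, whereas the protocol lists other reasons as well.
- A reader might infer that the sign of the result will reverse. For one patient it does so only below a best reduction of about 16.7% (higher for small sums). Group means under stopping at progression were near zero at an assumed −20% and remained reductions at −30%. Under the Group 1A/2A rule they remained reductions throughout.

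The rule for Group 3A is itself not uniform. The Study Summary gives progression or toxicity, while Section 3.2 has responders stop on decline to stable disease as well. Those passages need reconciling. If the Section 3.2 wording governs, Group 3A responders may stop earlier than the simulation assumes, and the gap in the last-scan value would be smaller.

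**Conclusion.** The inconsistency is established from the text: week 8, best to discontinuation, and an unnamed scan after treatment. It matters because regression is compared between Groups whose treatment ends under different rules. An end-of-treatment value, and to a lesser extent a best value, can create or reverse a naïve versus previously treated difference without any difference in the tumors.

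The single-patient arithmetic follows from the protocol's own progression rule, for progression exactly at the threshold: −10% becomes +8%, and −20% becomes −4%. The group-level figures show direction under assumed kinetics and are not a forecast. The ambiguity also arises within a patient, because Section 3.2 lets some stable-disease patients resume matched treatment after progressing on chemotherapy, so treatment can end twice. Best change is not wrong as an endpoint summary; it is unsuitable as the basis for this comparison. Severity is modest because the endpoint is exploratory.

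**What to change.** Delete the after-treatment wording in Sections 6.4 and 6.6. For the between-Group comparison, use percent change in the sum of target-lesion diameters from baseline to the first assessment at about week 8, as Section 1.3 hypothesizes. Report best percent change, as defined in Section 1.5, descriptively by Group and arm. Make the Study Summary (endpoint list and statistical methodology), Sections 1.3 and 1.5, and Sections 6.4 and 6.6 agree.

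No visit or scan is added, since imaging at about week 8 is already specified for both arms of every Group. There are two costs. Late shrinkage will appear only in the best-change summary. Patients with no week-8 scan, for instance after early death or toxicity, drop out of the comparison and must be counted and reported by Group and arm. Because the scan follows standard of care or another trial's schedule, its timing will vary, so one assessment window should be stated for all Groups.
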